### 5.5 STRATEGIES FOR RECRUITMENT AND RETENTION

*Study setting*

This study involves 20 neighborhoods and 21 clusters in the Pittsburgh area; within each neighborhood, one to four different community partner organizations (referred to as “community

partners” here) participated. Neighborhoods were recruited by identifying a potential community partner who could host the program and were willing to be randomized to receive the intervention or control programming. These community partners included youth-serving organizations, YMCA, Urban League, faith-based organizations, and libraries. Additionally, we partnered with the county’s community intensive surveillance program, a diversion program for youth involved in the juvenile justice system.

Neighborhoods were identified based on having sites where the YMCA, Urban League, or other youth serving partners had existing programs and which were considered lower income communities based on census information and school district data. Asset maps were created for each neighborhood with the goal of identifying community champions and youth-relevant resources to support this community-based project. The strong partnerships established with key stakeholders in each of these sites (including site coordinators, facilitators, and community members) facilitated recruitment and retention as described below.

Among the 20 participating neighborhoods, the proportion of students attending public high schools in those neighborhoods considered economically disadvantaged ranges from 32-100%; the high school graduation rate for those same school districts ranged from 63-97%. Each of these neighborhoods struggle with poverty, school ‘push-out’ (disciplinary actions that push youth, especially African American boys, out of the regular school system), and among the highest rates of gang and gun violence in the county (see Table 2 for neighborhood characteristics). These characteristics were compared by treatment arm using Kolmogorov-Smirnov two-sample exact tests due to their non-normal distributions. Neighborhood characteristics did not vary between the intervention and control arm neighborhoods.

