Within the 20 participating neighborhoods, there were a total of 40 sites/community partners/locations approached and 38 agreed to participate. The composition of the participating sites included 11 places of worship, 20 community centers, 2 public libraries, and 5 juvenile justice community intensive surveillance program centers. One site (cluster) was located at the downtown Urban League office and consisted of youth involved in an African American young men’s leadership group who came from several different neighborhoods and schools in the Pittsburgh area.

For recruitment of eligible youth, we rely on this network of community partners identified in asset maps created for each neighborhood cluster. This includes site leaders, program facilitators, recruiters with strong connections to their community, prevention specialists embedded in schools, school districts that offer community-based programs as an alternative to suspension, and the Community Intensive Supervision Program (CISP) for youth involved in the juvenile justice system.

Using respondent driven sampling (RDS), former and current participants may refer their friends to the program. Participants interested in RDS receive a packet of information on how to recruit a friend or neighbor and five recruitment coupons. When newly-recruited participants come to their first session and turn in their recruitment coupon, the peer recruiter is compensated \$5, up to \$25 overall.

Once community partners recruit youth, retention throughout the 18-hour curriculum is a key focus. Upon enrolling in either the control or experimental arm, prospective participants receive program information, sign an assent form and complete a contact information sheet. Research assistants ensure that the document is legible and that all fields are completed. Research assistants use this information to contact the participant prior to each session to remind them of the session. If youth are not present at the beginning of a session, research assistants and facilitators will contact the participant to encourage them to join late.

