#### 9.4.9 EXPLORATORY ANALYSES

We will also conduct two sets of exploratory analyses. First, we will conduct an intensity-adjusted analysis that reflects the actual delivery of the program. To achieve this, we will use a continuous score of “intensity” to replace the binary intervention variable in the models for the primary analysis. This score will be calculated for each round (program delivery) by using two sources of information. The first is information collected systematically about each session by trained research assistants who observed the sessions, including whether each task assigned to a module was performed (yes or no). The second is a summary measure of overall attendance for each round, tracked by using sign-in sheets with the research assistants. The second set will be a per-protocol analysis. This set of models will include only participants in the intervention arm that received the full intervention, defined as having covered a minimum threshold of tasks across the six sessions and having sufficient attendance. These measures replicate the intensity score values, but are then dichotomized to yes or no to receiving the full intervention. All control arm participants will be included in these models.

To explore whether demographics, youth pre-intervention risk and protective factors (e.g., history of SV/ARA exposure, sexual risk, connectedness), and site-level differences (e.g., staff experience, organizational capacity, intervention intensity) moderate the effect of the intervention on the primary and secondary outcomes, linear mixed models slightly different from those described above will be utilized. The outcome variables will be modeled as a function of the following variables: the outcome at baseline, the treatment group, the potential moderator, the interaction between the treatment group and moderator, and a random effect for cluster. A significant interaction suggests the presence of intervention effect heterogeneity, and we will follow the approach of Kraemer (53) by focusing on effect size derivation rather than formal hypothesis testing.

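### Aim 3's setting-level moderators get only a cluster random effect although they can vary between sites or rounds within a cluster, so their intervals may be somewhat too narrow

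*Protocol*

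**What the plan says.** Aim 3 (Sections 4.1 and 9.1) explores whether youth characteristics and setting-level characteristics are associated with differences in outcomes. Section 9.4.9 turns this into a model that asks, among other things, whether "site-level differences (e.g., staff experience, organizational capacity, intervention intensity) moderate the effect of the intervention". The terms are the baseline outcome, treatment group, moderator, "the interaction between the treatment group and moderator, and a random effect for cluster". No random effect for site or round is listed.

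Section 9.4.9 also defines the intensity score: "This score will be calculated for each round (program delivery"). Section 5.5 describes the settings: "within each neighborhood, one to four different community partner organizations" took part, with "40 sites/community partners/locations approached and 38 agreed to participate". Section 6.3 gives 21 randomized clusters, 11 experimental and 10 control.

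On interpretation, Section 9.4.9 says "A significant interaction suggests the presence of intervention effect heterogeneity", and in the same sentence commits to "focusing on effect size derivation rather than formal hypothesis testing".

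**The concern.** A cluster random effect protects a comparison of things that are constant within a cluster, and arm is one of them. A moderator that differs between two sites in the same neighborhood, or between two rounds, is compared partly within the cluster. There the stated model treats each youth as a separate observation of the moderator, although youth at one site share facilitators, sessions and peers. Section 5.5 also lets participants recruit friends, which makes shared-site correlation plausible.

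If that correlation exists, the interaction is reported more precisely than the data allow. At stake is how far the setting-level part of Aim 3 can be trusted when it points to conditions under which the program works better or worse.

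**Working it through.** The protocol gives no figure for the moderator analysis, so there is none to reproduce.

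**Inputs from the protocol.** 866 participants, 80% retention at Time 3 and a within-cluster ICC of 0.01 (Section 9.2); 21 clusters split 11:10 (Section 6.3); 38 sites, one to four partner organizations per neighborhood (Section 5.5).

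- Retained youth per cluster: 866 × 0.8 / 21 = 33.0.
- Retained youth per site: 866 × 0.8 / 38 = 18.2.
- Sites per cluster: 38 / 21 = 1.8 on average, so several clusters must hold more than one.

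**Assumed.** The extra site variance (as a share of total variance, beyond the cluster), varied from 0 to 0.05; the distribution of sites over clusters; a continuous outcome.

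**Rough guide.** Take a moderator that varies only within clusters, with cluster share c, extra site share s and m youth per site. A site mean has within-cluster variance s + (1 − c − s)/m. The cluster-only model allows for about (1 − c − s)/m. With c = 0.01 and m = 18.2:

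- s = 0.01: 0.98/18.2 = 0.0538, so the SE ratio is √(0.0538/0.0638) = 0.92.
- s = 0.05: 0.94/18.2 = 0.0516, so the SE ratio is √(0.0516/0.1016) = 0.71.

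This is roughly a worst case. A real moderator also varies between clusters, where the cluster effect helps, and the fitted variance terms absorb some of the site variance.

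**Simulation of the stated model** (no true interaction, moderator varying by site, cluster ICC 0.01, 8,000 runs per row):

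| Extra site variance | Model SE / true SE | Rejection, large-df test | Rejection, t on 17 df |
|---|---|---|---|
| 0 | 1.00 | 5.3% | 3.5% |
| 0.01 | 0.94 | 6.8% | 5.2% |
| 0.02 | 0.92 | 7.6% | 5.5% |
| 0.03 | 0.88 | 9.1% | 6.7% |
| 0.05 | 0.82 | 11.1% | 8.6% |

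The 17 df are 21 clusters less 4 coefficients (intercept, arm, moderator, interaction). A second simulation, also on an assumed layout, gave SE ratios of 0.92, 0.90 and 0.81 and large-df rejection of 7.1%, 7.2% and 11.8% at extra site variance 0.01, 0.02 and 0.04.

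**If the planned ICC of 0.01 comes wholly from shared sites.** With about 43% of within-cluster pairs sharing a site (layout assumption), the site variance is about 0.01/0.43 = 0.023. Simulations at 0.024 with no cluster variance rejected 8.3% to 9.3% with a large-df test.

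**Effect of adding a site term alone.** In 1,500 runs per row, both models were fitted to the same data with the same large-df test. Rejection went from 4.6% to 4.2% at extra site variance 0, 5.5% to 4.5% at 0.01, 9.8% to 7.0% at 0.03, and 10.4% to 6.1% at 0.05. The SE ratio with the site term was between 0.93 and 1.04. Monte Carlo error is about √(0.05 × 0.95/1500) = 0.6 points.

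**If the moderator is constant within a cluster.** The stated model rejected 5.3% to 6.5% across extra site variance 0 to 0.05 (2,000 runs per row), so the cluster effect largely suffices.

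**The case against.** Four points count against a strong version of this concern.

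- **No site-level correlation is documented.** A reader might infer that the intervals are certainly too narrow and that heterogeneity will be found too often. The protocol does not support that. It gives only a within-cluster ICC, and if all correlation is at that level nothing is inflated. This stands, and the point is conditional.
- **The protocol sometimes uses site to mean cluster.** Section 9.2 speaks of about 41 boys per site, which is 866/21 = 41.2 and not 866/38 = 22.8. Section 5.5 equates one site with a cluster. If the moderators are scored once per cluster, the model is at about the right level. This also stands, but the protocol does not say how several organizations would become one cluster value, and intensity is scored per round on either reading.
- **Part of the excess rejection is a matter of reference distribution.** The protocol does not prescribe a large-df test. In the table, 17 df brings rejection to 5.2-5.5% at extra site variance 0.01-0.02. At 0.05 it remains 8.6%, and the choice of df does not correct the standard error itself. For the case where the planned ICC is wholly from sites, results on 17 df ranged from about 5% to 7%.
- **The analysis is exploratory and centred on effect sizes.** That limits the harm. It does not remove it, because intervals around effect sizes inherit the understated standard error, and Section 9.4.9 still attaches meaning to a significant interaction.

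**Conclusion.** The point holds conditionally and is minor. The stated model has no term for the level at which some of its own moderators are measured. If youth sharing a site or round are correlated beyond the cluster, the interaction's standard error is about 6-8% too small at extra site variance 0.01 and 18-19% too small at 0.04-0.05. Large-df rejection is then about 7% and 11-12%. At zero extra variance there is no inflation. These figures rest on an assumed site variance, an assumed layout of 38 sites and a continuous outcome; the binary primary outcome was not simulated.

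A reader might carry the concern over to the main result. That would be wrong: arm is constant within a cluster, so the primary arm effect is not at issue, and neither are the youth-level moderators of Aim 3.

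**What to change.** In Section 9.4.9:

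1. State whether site, for Aim 3, means partner location or randomized cluster. If it means cluster, say how values from several organizations or rounds are combined.
2. For any moderator measured below the cluster, add a random effect at the level of measurement, nested in cluster: site for staff experience and organizational capacity if they are recorded by partner location, round for intensity. A site term alone would not cover intensity.
3. Base degrees of freedom for those interactions on the number of such units, for example about 38 − 4 = 34 for a site-level moderator.
4. Keep the cluster-only model for youth-level moderators and the primary analysis.

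The cost is a sentence or two of text and somewhat wider intervals for these moderators. The identifiers should already exist: Section 6.1.2 records attendance by site and round, and the planned intensity analysis has to link youth to rounds.

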## 10 SUPPORTING DOCUMENTATION AND OPERATIONAL CONSIDERATIONS

### 10.1 REGULATORY, ETHICAL, AND STUDY OVERSIGHT CONSIDERATIONS

#### 10.1.1 INFORMED CONSENT PROCESS

##### 10.1.1.1 CONSENT/ASSENT AND OTHER INFORMATIONAL DOCUMENTS PROVIDED TO PARTICIPANTS

###### **Assent and Consent**

Adolescent males ages 13-19 receive a description about the research study and parental letter about the study from the community sites. The parent letter includes an option for parents/caregiver to decline their child's participation. We received a waiver of parental permission and waiver of signed consent from the University of Pittsburgh Human Subjects Research Protection Office. Research assistants review the verbal assent/consent form with youth at the beginning of the first session and answer any questions pertaining to confidentiality, the program flow, and survey time points. The consent information sheet covers all 3 waves of data collection, Time 1 through Time 3 as described earlier.

##### 10.1.1.2 CONSENT PROCEDURES AND DOCUMENTATION

A waiver to document informed consent and a waiver for parental permission were granted by the IRB.

#### 10.1.2 STUDY DISCONTINUATION AND CLOSURE

N/A

#### 10.1.3 CONFIDENTIALITY AND PRIVACY

Participant confidentiality and privacy is strictly held in trust by the participating investigators, their staff, the safety and oversight monitor(s), and the sponsor(s) and funding agency. This confidentiality is extended to the data being collected as part of this study. Data that could be used to identify a specific study participant will be held in strict confidence within the research team. No personally-identifiable information from the study will be released to any unauthorized third party without prior written approval of the sponsor/funding agency.

All research activities will be conducted in as private a setting as possible.

The study monitor, other authorized representatives of the sponsor or funding agency, representatives of the Institutional Review Board (IRB), or regulatory agencies, may inspect all documents and records required to be maintained by the investigator.

The study participant's contact information will be securely stored with the research team for internal use during the study. At the end of the study, all records will continue to be kept in a secure location for as

long a period as dictated by the reviewing IRB, Institutional policies, or sponsor/funding agency requirements.

Study participant research data, which is for purposes of statistical analysis and scientific reporting, will be stored in the research team's secure, password protected electronic database. This will not include the participant's contact or identifying information. Rather, individual participants and their research data will be identified by a unique study identification number (using the secret code generated by participants).

#### Measures Taken to Ensure Confidentiality of Data Shared per the CDC Data Sharing Policies

It is CDC policy that the results and accomplishments of the activities that it funds should be made available to the public. The PI will ensure all mechanisms used to share data will include proper plans and safeguards for the protection of privacy, confidentiality, and security for data dissemination and reuse (e.g., all data will be thoroughly de-identified and will not be traceable to a specific study participant). Plans for archiving and long-term preservation of the data will be implemented, as appropriate.

#### Certificate of Confidentiality

To further protect the privacy of study participants, the PI received a certificate of confidentiality from the Centers for Disease Control and Prevention. Investigators and others who have access to research records will not disclose identifying information except when the participant consents or in certain instances when federal, state, or local law or regulation requires disclosure. NIH expects investigators to inform research participants of the protections and the limits to protections provided by a Certificate issued by this Policy.

**Data Security:** Responses to the anonymous web-based secure survey are entered by the youth participants themselves through a computer-based system; the data are automatically entered into a password protected data base accessible only to the investigative team. No names are connected to the survey data as each participant creates their own secret code as described above. The only study documents that will contain unique personal identifiers are consent forms and the contact list of participants that are kept to assist with re-contacting participants at the end of the intervention (Time 2) and in the subsequent year (Time 3).

Contact forms will be stored in a secure file drawer inside the locked office of the PI's research lab whenever not in use. Contact forms will be stored separately from any survey data collected in this study (the survey data are collected via computer and immediately housed in a password-protected secure database). The names of participants will be kept in an encrypted file on a password protected secure on-line server (available to the research team through the University of Pittsburgh), and accessed only when needed to arrange the follow up data collection with each community site (Time 2 and Time 3). Please note that there are three layers of protection for the contact information: password protection to enter the University of Pittsburgh system, a username that has been granted access to the secure drive, and another password to decode the encrypted file. This information will be accessed only when needed to arrange follow up contact with participants and scheduling data collection.

---

#### 10.1.4 FUTURE USE OF STORED SPECIMENS AND DATA

Data collected for this study will be analyzed and stored at the University of Pittsburgh in [name] (PI) research office, on a password protected, encrypted, secure drive. After the study is completed, the de-identified, archived data will be made available to interested researchers 12 months after publication of the intervention manuscript.

---

### 10.1.6 SAFETY OVERSIGHT

As a minimal risk study, safety oversight is under the direction of the PI and an internal safety monitoring group including the study coordinator and study statistician.

---

### 10.1.7 CLINICAL MONITORING

Extra precautionary measures are taken to protect the data, including the use of a personally created ID code to maintain anonymity of the survey data and an internal data safety and monitoring plan, which includes the following:

- a) Systematically review assessment materials to ensure that assessment is conducted appropriately and that participants disclosing abuse or violence during the course of taking the survey receive appropriate connection to violence-related services and that mandated reports are made by site personnel when appropriate.
- b) Systematically review notes from research assistants to ensure that participants experiencing distress are being connected directly with the site directors and youth workers, receiving educational materials, and being referred appropriately; this includes ensuring that all research assistants document asking each participant about emotional distress after completion of the survey.
- c) Monitor staff performance with regard to protection of privacy, confidentiality, maintenance of secure data bases, and study procedures designed to reduce the risk of distress and potential breaches of confidentiality.
- d) Ensure that the PI ([name]), or a designated qualified individual, will be available by pager in case research staff needs to confer regarding participants' behaviors or comments made during a survey or other research activities.
- e) Ensure that the PI ([name]), or a designated qualified individual, will be available by pager in case educators or violence prevention advocates from Center for Victims and Pittsburgh Action Against Rape, needs to confer regarding participants' or youth workers' behaviors or comments made during study implementation (i.e., during training, survey administration, or follow up contact with site administrators, youth workers and facilitators).
- f) Review and report any adverse events associated with the study.

---

#### 10.1.8 QUALITY ASSURANCE AND QUALITY CONTROL

Quality control (QC) procedures will be implemented as follows:

**Informed consent** --- Study staff will review the verbal consenting process. This review will evaluate compliance with GCP, accuracy, and completeness. Feedback will be provided to the study team to ensure proper consenting procedures are followed.

**Source documents and the electronic data** --- Data will be initially captured on source documents (see **Section 10.1.9, Data Handling and Record Keeping**) and will ultimately be entered into the study database. To ensure accuracy, staff will compare a representative sample of source data against the database, targeting key data points in that review.

**Intervention Fidelity** — Consistent delivery of the study interventions will be monitored throughout the intervention phase of the study. Procedures for ensuring fidelity of intervention delivery are described in **Section 6.2.1, Interventionist Training and Tracking**.

**Protocol Deviations** – The study team will review protocol deviations on an ongoing basis and will implement corrective actions when the quantity or nature of deviations are deemed to be at a level of concern.

Should independent monitoring become necessary, the PI will provide direct access to all trial related sites, source data/documents, and reports for the purpose of monitoring and auditing by the sponsor/funding agency, and inspection by local and regulatory authorities.

---

